### Study population

#### Randomised controlled trial

##### Inclusion criteria – general practices

General practice populations in disadvantaged areas of North East England, including urban, rural and semi-rural areas, with no previous access to targeted welfare rights advice services delivered to primary care patients, will be included. All practices from participating social service districts will be ranked according to deprivation score (2010 English Index of Multiple Deprivation calculated at Middle Super Output Area level for practice postcodes, according to the method of Griffin et al [46].). Those practices in the lower two fifths of the deprivation ranking distribution without existing dedicated or targeted welfare rights advice services will be eligible for inclusion.

##### Inclusion criteria - patients

· Volunteer men and women registered with a general practice in one of 10 social services areas (1 individual per household)

· Aged ≥60 years

· Providing informed consent

##### Exclusion criteria - patients

· Resident in social care (residential) or nursing homes or hospitals at the time of identification and recruitment

· Diagnosed with terminal illness

· Cannot participate in the research by virtue of current physical/mental health

· Lack of fluency in written and spoken English

#### Qualitative study

A range of professionals involved in service commissioning, policy and strategy will be interviewed including: (i) public health/NHS (GP commissioning consortia); (ii) social and welfare rights services; (iii) Pension Service, Department for Work and Pensions; and (iv) the voluntary sector. Trial participants will also be purposively selected to take part in interviews (see below).

### Screening, recruitment, consent and randomisation

#### Identification and screening of trial participants

Practices will be recruited with the help of the Northern and Yorkshire Primary Care Research Network (PCRN-NY). The study will take place in 10 local authority districts (Stockton, Darlington, Middlesbrough, County Durham, Sunderland, South Tyneside, North Tyneside, Newcastle, Gateshead, Northumberland) which have agreed to provide welfare rights advice services. We plan to recruit two general practices per local authority district. Potentially eligible practices will be identified as described above. We will then liaise with Welfare Rights Services to establish whether any of these practices have existing dedicated or targeted welfare rights advice services, since this will render them ineligible. Next, we will ask the PCRN-NY to identify which of the practices still eligible have indicated willingness to participate in research. If more than two general practices from each list have expressed willingness to participate in research, we will order the remaining practices randomly and then contact them sequentially until two practices from each social services district have agreed to participate in the trial.

General practices in North East England have access (via PCRN-NY and the Comprehensive Local Research Networks (CLRNs)) to personnel and financial resources to identify and approach research study participants. Using PCRN-NY and CLRN personnel and financial resources, each participating practice will be asked to generate a random sample of up to 300 people aged ≥60 from their practice register. Practice staff will scrutinise their list to identify any patients terminally ill and patients known to be resident in hospital or long-term care, who will be excluded. They will also check to ensure that only one person per household has been selected for this list. If 2 or more people from the same address are found, one will be selected at random to be retained and the other(s) removed from the sample list.

#### Recruitment

This list of up to 300 names per practice will be randomly ordered and the first 100 patients on the list will be sent a letter and study information sheet by their GP, inviting participation in the trial. The letter will explain that, unless the participant objects (by returning an opt-out form to the practice within 2 weeks), their name and contact details will be passed to the research team, who will then contact them directly to discuss the trial further and seek informed consent. Patients’ views have been incorporated in the design of patient information sheets and consent forms and the opt-out approach has been approved by the Research Ethics Committee.

After two weeks, contact details of those who have not opted out will be passed to the research team. Research staff will contact these individuals and, if acceptable, arrange a face-to-face meeting at a mutually convenient time in the participant’s own home or another location of the participant’s choosing.

Our target for recruitment from each practice will be predetermined (depending on the final number of practices involved) in order to achieve the total sample. If this number is not achieved from the first 100 mailed, subsequent mailings of further names from the list of up to 300 will take place until the required number have been recruited. The number to be included in subsequent mailings will be determined by the number of responses already received (i.e. the yield rate of each wave of invitations). Since recruitment interviews will be spread over a six month period, this iterative recruitment process should not delay overall recruitment.

#### Consent

At the initial appointment, the research interviewer will first seek written, informed consent and then, if appropriate, proceed to collect baseline data. Interviewers will communicate in English, and if English is not the first language of any participant and (s)he is unable to speak it fluently, the participant will be excluded from the study. Friends, relations or carers will not be used as interpreters and interpreting services available to WR Advisors from local authorities will not be available for research interviews (the CASP19 has not been translated to other appropriate languages nor cross-culturally validated).

The researcher will assess if an individual has the capacity to consent. If it is established that an individual is unable to provide written consent because of literacy, vision or motor problems, it will be arranged for verbal consent to be taken in the presence of an independent witness (e.g. family member) who will initial, sign and date the consent form on the participant’s behalf.

Although unlikely to be a frequent occurrence, it is conceivable that a participant may lose mental capacity *during* the follow up period. We will explain to participants at baseline that, if this happens, we will retain the information that we gathered prior to his/her loss of capacity. The investigator and research interviewers will undertake all reasonable steps to protect the study participant. In accordance with the Mental Capacity Act 2005, nothing will be done to the person to which he or she appears to object (whether by showing signs of resistance or otherwise) except where what is being done is intended to protect him or her from harm or to reduce or prevent pain or discomfort.

#### Identification and recruitment of participants for qualitative sub-study

Interviews with approximately 30 purposively sampled trial participants will take place between 8–11 months and between 20–23 months from baseline (approximately 15 interviews in each period). Trial participants will be identified through the trial database and recruited to achieve a maximum variation sample with respect to group allocation, gender, age, benefit entitlements and any unanticipated consequences of the intervention identified at 12 month follow-up.

A sample of approximately 10 professionals/stakeholders will also be interviewed at 20–23 months from baseline. Stakeholders will include representatives of the Department for Work and Pensions, Benefits Agency, adult social services managers, welfare rights advisors, General Practitioners (GPs), primary care commissioners and directors of public health.

Trial participants will be asked during baseline assessment and consent procedures if they would be willing to participate in the qualitative interviews. Those selected for interview (trial participants and professionals/stakeholders) will be sent a letter of invitation and additional participant information sheet by the research team. Contact details for the researchers will be provided so that those approached to participate can ask any questions they may have before coming to a decision on participation. Separate informed consent will be taken for the interviews and lack of consent to participate in this element of the research will not prevent trial participants from continuing in the trial.

Sampling and interviews with both groups will continue until data saturation is achieved [47]. Interviews with trial participants will explore: acceptability of the intervention and research design; unanticipated consequences of the intervention; and perceived impacts of the intervention. Interviews with stakeholders will explore: acceptability of the intervention, training and research; fidelity of the intervention; and likely implications of the intervention for translation into routine policy and practice, both within the North East and more widely.

### Sample size

#### Trial sample size and power

A minimum of 750 participants will be randomised to intervention and control arms, providing 90 % power at 5 % significance level to detect a 1.5 unit difference in mean CASP19 score [35,36] between intervention and control groups, assuming a standard deviation of 8.7 and a correlation between baseline and 24 months of 0.74 [48], and 15 % attrition over 24 months (as experienced in our pilot RCT) [7]. There has been no published work to establish a meaningful or clinically important difference on the CASP19 scale. However, we have used data from two waves of the English Longitudinal Study of Ageing in those aged ≥60 yrs to investigate the adjusted mean difference in CASP19 at Wave 2 between groups whose social or health circumstances had changed [48].

Examples of changes in CASP19 score associated with changes in health or social circumstances that we might expect to see in the proposed trial include: ‘developed limiting illness’ -2.8 units; ‘developed depression’ -2.7units; ‘lost access to car’ -1.8 units; ‘increased chance will not meet financial needs’ -1.1 units. These differences on the CASP19 scale suggest that a difference of 1.5 units would represent a ‘clinically’ important difference.

The chosen sample size should also provide power to demonstrate some clinically significant differences in secondary outcomes. For example, 750 participants will provide 90 % power to detect a difference between a prevalence of 11 % and 4 % of clinically significant depressive symptoms (PHQ-9 score ≥10).

#### Qualitative sub-study sample size

Sample size for the qualitative sub-study will be determined by data saturation. We anticipate that up to 30 trial participants and up to 10 stakeholders will be included.

### Study intervention details

#### Intervention

Welfare rights advice consultations and active assistance with benefit claims will be offered and delivered in participants’ own homes, tailored to individual needs by a trained WR Advisor employed by a local authority or Citizens’ Advice Bureaux (CAB) in North East England. Following randomisation, intervention group participants will be given an appointment in their own home with a WR Advisor within 2 weeks, during which participants will undergo a full benefit entitlement assessment involving: assessment of financial, material and welfare status; assessment of previous benefit entitlement and claims; discussion of current entitlement and options for action, including new claims (financial and non-financial). Active assistance with benefit claims and other welfare issues will be given. Complex claims or those referred for further assessment or tribunal will be managed in the usual way by WR Advisors. Participants will be followed up intermittently by WR Advisors until they no longer require assistance (cases are usually ‘closed’ once all claims and appeals have been resolved satisfactorily). It is expected that approximately 50 per cent of claims will be resolved within 3 months, but some may take up to 12 months [7]. The intervention will be funded and provided by WR Advice departments and CAB in 10 local authority areas across the North East by trained WR Advisors.

The North East Strategic Health Authority has provided funding for training of WR Advisors to ensure a consistent approach to delivery of the intervention. Such training was delivered in the context of our pilot RCT [7,8] and Newcastle City Council, Welfare Rights Service has agreed to provide similar training for this trial.

#### Comparator (wait-list control condition)

Participants randomised to the control group will receive ‘usual care’ from both health and social services after randomisation until they have completed their 24-month follow-up assessment. They will be given no advice regarding welfare rights as a part of the study intervention during this period. However, they may independently seek welfare rights advice from the local authority, CAB or voluntary sector organisations. If this occurs, they will remain in the trial, but details of such advice and ensuing claims and outcomes will be recorded at the 24 months follow-up assessment. Following their 24-month follow-up assessment, they will receive the intervention, as delivered to the intervention group (described above), including all follow-up visits by WR Advisors and assistance with claims and appeals over the following months, until all claims have been resolved.

### Long-term care

Both intervention and control group participants will remain clients of the welfare advice service beyond the end of the trial, if necessary, until such time as their help is no longer needed, as per usual welfare rights advice service protocols.

### Randomisation

Following baseline measurements, participants will be randomised in a 1:1 ratio to intervention or control condition. Research interviewers will notify the project administrator after each baseline interview that a new participant has been successfully recruited. The administrator will hold sequential allocation tables for each practice, independently generated from random numbers prior to recruitment. The administrator will allocate all participants to intervention or control group in the sequence that they are recruited and immediately send each participant a standard letter informing them of their group allocation. The administrator will also immediately inform the appropriate WR Advisor of the contact details of each newly allocated intervention group participant and indicate that they are to be seen within 2 weeks. WR Advisors will be sent lists of control group participants to assess 24 months later. The research interviewers will not be notified of allocation status to ensure that they remain blinded for the duration of the study.

### Study data

#### Data handling and record keeping

Study data will be entered directly into a secure database during interviews for processing and management, and a record of any changes made to the data post-entry will be maintained. All personal information obtained for the study will be held securely at Newcastle University and will be treated as strictly confidential. Entry and verification of twelve month data from self-completion questionnaires will be outsourced to a data entry company.

 Data collection and transfer in this study will comply with UK NHS Research Ethics Service (NRES) http://www.nres.npsa.nhs.uk/ and Caldicott guidelines http://www.dh.gov.uk/en/Managingyourorganisation/Informationpolicy/Patientconfidentialityandcaldicottguardians/DH_4100563 and the Data Protection Act (1998) http://www.dh.gov.uk/en/Managingyourorganisation/Informationpolicy/Recordsmanagement/DH_4000489. All patients will be allocated a unique study identifier, which will be used on all data collection forms and questionnaires to preserve confidentiality; names or addresses will not appear on completed questionnaires or other data collection forms. Only a limited number of members of the research team will be able to link the unique identifier to patient-identifiable details (name, address and telephone number) which will be held on a password-protected database. All study documentation will be held in secure offices, not open to the public and all members of the research team with access to identifiable or anonymised data will operate to a signed code of confidentiality. Transmission of original or hard copy records (e.g. questionnaires, interview recordings) will be by secure fax, post or hand delivery by members of the research team or by the WR Advisors. Participants will be informed in the patient information sheet about the transfer of information to the research team and about levels of access to patient identifiable data, and will be asked to consent to this. Any data used in publications from the Do-Well study will be fully anonymised; it will not be possible to identify individual patients from such publications.

At the end of the study, original questionnaires, interview transcripts and consent forms will be securely archived for 15 years following publication of the last paper or report from the study, in line with Sponsor policy and Newcastle Clinical Trials Unit (NCTU) standard operating procedures. This will also allow any queries or concerns about the data, conduct or conclusions of the study to be resolved. Both sets of data will be archived after 5 years. Anonymised data will be submitted to a national archive collection.

#### Statistical analyses

Analyses of covariance and regression methods will compare primary and secondary outcomes between intervention and control groups at 24 months, adjusting for baseline outcome values and any imbalance in other covariates as appropriate.

Analyses will be by intention-to-treat. It will be necessary to consider any difference in attrition rates, and the non-randomness of the attrition, when comparing quality of life between the two groups. In the pilot RCT only 7/126 (5.5 %) died during the 24 month follow-up, so it is thought unlikely that methods for joint modelling of survival and longitudinal data will be necessary.

Exploratory sub-group analyses will also be undertaken, for example to examine differences in outcome between men and women, by age and by amount and type of benefits received.

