### Generalisability

Our pilot trial was undertaken in one social services district (Newcastle upon Tyne) and in 4 general practice populations [7]. However, we know, from other work and discussions locally, that service delivery in welfare rights advice varies from area to area, as do general practice populations. To enhance the potential generalisability of the results, the RCT will therefore be undertaken across a range of geographical and local authority areas (including urban and rural) and general practices. It is possible, indeed likely, that the present welfare regime will change during the course of the trial. The proposed intervention is not dependent on any particular set of benefits and is adaptable to any new regime. This adds to its future generalisability.

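### The stated 90% power makes no allowance for variation in the treatment effect between advisors or services, which group the intervention arm alone

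*Protocol article*

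**What the plan says.** Protocol article, Trial sample size and power: the trial is to randomise at least 750 people, a size described as "providing 90 % power at 5 % significance level to detect a 1.5 unit difference in mean CASP19 score". The inputs are an SD of 8.7, a baseline-to-follow-up correlation of 0.74 and 15% attrition. No ICC or design effect enters.

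Intervention: the advice is tailored to each person by a trained advisor and is "provided by WR Advice departments and CAB in 10 local authority areas across the North East". The number of advisors is not given. Common training is funded to make delivery consistent.

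Comparator: controls get no study advice until after their 24-month assessment.

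Randomisation: individuals are allocated 1:1 from separate tables for each practice, so both arms occur in every practice and district.

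Statistical analyses: "Analyses of covariance and regression methods will compare primary and secondary outcomes between intervention and control groups at 24 months", adjusted for baseline values and for any imbalance in covariates. No practice, service or advisor term is named.

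Generalisability: "service delivery in welfare rights advice varies from area to area", which is given as a reason for running the trial across many areas.

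**The concern.** Until the primary outcome is measured, contact with a study advisor happens in one arm only. The design is therefore partially nested: intervention participants share providers and controls do not. If some advisors or services achieve more than others, outcomes of intervention participants with the same provider are correlated, and the variance of the intervention mean exceeds the independent-observations value. A practice main effect does not absorb this, because the variation is in the treatment effect.

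The discussion of study design considers clustering only as a reason to prefer individual to cluster randomisation. Clustering that arises from delivery is not considered. The pilot ran in one district, so it could not have informed variation between districts' services.

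Two things are at stake: whether the 90% is a fair description of the trial's chance of detecting 1.5 units, and whether the interval for the primary result is wide enough if it is meant to apply beyond the participating services.

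**Working it through.** **Reproducing 750.** Inputs from the sample-size section: difference 1.5, SD 8.7, correlation 0.74, attrition 15%, power 90%, 5% level (two-sided assumed; a one-sided test gives 615).

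- Residual SD = 8.7 × √(1 − 0.74²) = 5.852.
- n per arm = 2 × (1.960 + 1.282)² × 5.852² / 1.5² ≈ 320, so 640 analysed.
- 640 / 0.85 = 753 randomised, against 750 stated.
- At 750: 637.5 analysed, 318.75 per arm. SE = 5.852 × √(2/318.75) = 0.4635. Power = Φ(1.5/0.4635 − 1.96) = 89.9%.

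The stated size is reproduced without a design effect, so it contains no hidden allowance for clustering.

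**Adding provider variation in the intervention arm only.** With K providers, m = 318.75/K and an ICC on the baseline-adjusted scale:

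SE = 5.852 × √([1 + (m − 1) × ICC]/318.75 + 1/318.75); power = Φ(1.5/SE − 1.96).

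Example, K = 10 and ICC 0.01: m = 31.9, design effect 1.309, SE = 5.852 × √(2.309/318.75) = 0.498, power = Φ(3.012 − 1.96) = 85.4%.

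The ICCs are assumptions. K = 10 matches the ten areas; 20 and 30 stand for assumed numbers of advisors. The last column holds K fixed.

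| Providers | ICC | SE relative to independent | Power at 750 | Randomised for 90% |
|---|---|---|---|---|
| any | 0 | 1.00 | 89.9% | 753 |
| 10 | 0.01 | 1.07 | 85.4% | 892 |
| 10 | 0.02 | 1.14 | 80.8% | 1097 |
| 10 | 0.05 | 1.33 | 68.1% | 3662 |
| 20 | 0.01 | 1.04 | 87.7% | 815 |
| 20 | 0.02 | 1.07 | 85.5% | 888 |
| 20 | 0.05 | 1.17 | 78.9% | 1224 |
| 30 | 0.01 | 1.02 | 88.5% | 793 |
| 30 | 0.02 | 1.05 | 87.1% | 836 |
| 30 | 0.05 | 1.11 | 82.8% | 1003 |

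These use the normal approximation. Small-sample degrees of freedom would lower them; with 10 services, a conservative 9 degrees of freedom gives 76%, 71% and 58% at ICC 0.01, 0.02 and 0.05 (82% at ICC 0).

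**What the ICC means in CASP-19 units.** The SD of provider effects is √ICC × 5.852: 0.59, 0.83 and 1.31 units at ICC 0.01, 0.02 and 0.05. The last is close to the 1.5-unit target, so 0.05 is a demanding upper value.

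**Shared and provider-specific effects.** A simulation used 10 services with 32 participants per arm in each, ICC 0.01 to 0.05, and a test that ignored service. A service effect common to both arms left type I error at 4.9% to 5.1% and power at 90% to 91%. A service effect in the intervention arm only, varying around zero, gave type I error of 6.6%, 8.9% and 14.0%. The formula 2 × [1 − Φ(1.96 × 0.4635/SE)] gives 6.8%, 8.7% and 14.1%. With 30 advisors the formula gives 5.6%, 6.1% and 7.8%.

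**The case against.** A reader might infer that the planned standard error is simply too small and the test anti-conservative. The protocol does not support that as a fact, for four reasons.

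- The analysis section states no independence assumption. Regression methods can include a multilevel model, and a statistical analysis plan that is not shown may specify one. This stands, and it is why the firm part of the point is the power claim, which the protocol itself fixes.
- A reader might also take any intra-service correlation to be harmful. Allocation is within practice, so effects shared by both arms largely cancel, as the simulation shows. Only variation in the treatment effect between providers matters.
- If advice has no effect on anyone, this mechanism does not inflate type I error. Inflation needs provider effects that average to zero, with some services lowering CASP-19. At ICC 0.05 with mean zero, about one service in five would lower it by 1.1 units or more (Φ(−1.1/1.31) ≈ 0.20), and nothing in the protocol suggests this. The type I figures are therefore conditional.
- Common training may reduce provider variation. With many advisors and a small ICC the loss is slight: 88.5% with 30 advisors at ICC 0.01.

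Treating the ten named districts' services as fixed is also defensible in a pragmatic trial. The result then describes the average effect in those services, and between-service variation need not enter its standard error. Against this, the protocol spreads the trial over areas to widen generalisability and envisages wider provision if health benefits are shown. Which inference is meant should be stated.

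**Conclusion.** The point holds as a matter of the power statement and of stating how provider variation is handled. The 750 is the independent-observations size with no slack, so the 90% applies only with no provider-specific variation in effect. That condition sits poorly with the protocol's own remark that delivery varies by area.

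The size is uncertain because both the ICC and the number of advisors are assumed. For ICC 0.01 to 0.05, power at 750 randomised runs from 85% down to 68% with 10 services and from 88.5% down to 83% with 30 advisors.

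If the inference is meant to reach beyond the participating services, an analysis of covariance that ignores this variation would give too narrow an interval, with a true SE about 2% to 33% larger over these assumptions. It is not established that the planned analysis will ignore it, nor that the variation is material.

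**What to change.** - In Trial sample size and power, say that the 90% applies with no provider-specific variation in effect, and give the power range for ICC 0 to 0.05 at the expected number of services or advisors.
- Include practice, the unit of the allocation tables, as a covariate in the primary analysis of covariance.
- Record the advisor and service for every intervention case.
- Before outcomes are seen, name a sensitivity analysis of the primary outcome: a partially nested mixed model with baseline CASP-19 and practice as covariates, a random provider effect in the intervention arm only, arm-specific residual variance and small-sample degrees of freedom.
- State whether inference is to the participating services or beyond them.

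Making the nested model primary is a trade-off and is not required here. The cost is modest: the administrator already notifies the relevant advisor at allocation and advisors already log visits, so provider identity should be obtainable without burden on participants. The downside is a wider interval in the sensitivity analysis, by the amount given above and somewhat more with few degrees of freedom, and a less favourable stated power.

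### The 24-month model picks covariates by observed baseline imbalance and does not name general practice, although allocation lists are held separately by practice

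*Protocol article*

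**What the plan says.** The Statistical analyses section of the protocol article compares primary and secondary outcomes at 24 months by analysis of covariance and regression, "adjusting for baseline outcome values and any imbalance in other covariates as appropriate". It names no covariate other than the baseline value of the outcome, does not define imbalance, and does not mention general practice.

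The Randomisation section says: "The administrator will hold sequential allocation tables for each practice, independently generated from random numbers prior to recruitment". Individuals are allocated 1:1. No blocking or other balancing within a practice's list is described. The section on identification and screening says "We plan to recruit two general practices per local authority district", and there are ten districts, so about 20 lists.

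The Generalisability section records that "service delivery in welfare rights advice varies from area to area, as do general practice populations".

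**The concern.** There are two linked weaknesses.

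1. **The covariate rule.** With individual randomisation, a baseline difference between arms arises by chance. A covariate improves the comparison by predicting the 24-month score, whether or not it happens to be imbalanced. A rule triggered by imbalance therefore lets the data choose the model, and it does not choose on the property that matters. With no candidate list and no definition, the wording leaves more than one possible primary result.

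2. **Practice.** It is the unit by which the lists are held, and the protocol itself expects practice populations and local services to differ. If the lists are balanced within practice, the arms will have nearly equal numbers in each practice, so practice will not look imbalanced and the rule will tend not to bring it in. That is also the case in which omitting practice gives a standard error that is too large.

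At stake are an avoidable dependence of the primary model on the data and, under stated conditions, a little lost power.

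**Working it through.** **Inputs from the protocol.** Sample size section: 750 randomised, "providing 90 % power at 5 % significance level to detect a 1.5 unit difference in mean CASP19 score", "assuming a standard deviation of 8.7 and a correlation between baseline and 24 months of 0.74", and 15% attrition. About 20 practices (2 × 10). The 5% level is taken as two-sided.

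**Inputs not in the protocol (assumed).** Equal practice sizes, and a residual practice ICC after baseline adjustment of 0.01 to 0.10.

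**Step 1: reproduce the stated sample size.**
- Residual SD = 8.7 × √(1 − 0.74²) = 5.852.
- n per arm = 2 × (1.960 + 1.282)² × (5.852/1.5)² ≈ 320, so 640 in total.
- Allowing for attrition: 640/0.85 = 753, against 750 stated.
- With 750 × 0.85 = 637.5 completers (318.75 per arm), power is 0.899. The stated figure reproduces.

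**Step 2: omit practice, lists balanced within practice.** The model without practice reports SE = 5.852 × √(2/318.75) = 0.4635. Balance removes the between-practice variance from the treatment contrast, so the true SE = 0.4635 × √(1 − ICC). Then:
- excess width = 0.4635/SE_true − 1
- actual type I error = 2 × [1 − Φ(1.96 × 0.4635/SE_true)]
- power without practice = Φ[(1.5 − 1.96 × 0.4635)/SE_true]
- power with practice = Φ[1.5/SE_true − 1.96]

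| ICC | True SE | Reported SE too wide by | Type I error | Power without practice | Power with practice |
|---|---|---|---|---|---|
| 0.01 | 0.4612 | 0.5% | 0.049 | 0.900 | 0.902 |
| 0.02 | 0.4589 | 1.0% | 0.048 | 0.901 | 0.905 |
| 0.05 | 0.4518 | 2.6% | 0.044 | 0.905 | 0.913 |
| 0.10 | 0.4397 | 5.4% | 0.039 | 0.911 | 0.927 |

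Simulated trials (20 practices of 32 completers, 3,000 null trials per setting) gave mean SEs with practice in the model of 0.4583, 0.4513 and 0.4393 at ICC 0.02, 0.05 and 0.10. These agree with the true SEs above.

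**Step 3: omit practice, lists unblocked.** In the same simulation with simple random allocation, the model without practice was not biased. Type I error was 0.046 to 0.051 over ICC 0 to 0.10, and the mean SE was 0.462 to 0.463 against an observed spread of 0.453 to 0.465. Adding fixed practice terms changed the mean SE as follows:

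| ICC | Without practice | With practice | Change |
|---|---|---|---|
| 0 | 0.4630 | 0.4701 | 1.5% wider |
| 0.02 | 0.4631 | 0.4658 | 0.6% wider |
| 0.05 | 0.4627 | 0.4587 | 0.9% narrower |
| 0.10 | 0.4618 | 0.4460 | 3.4% narrower |

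With unblocked lists, then, precision is lost by omitting practice only when the ICC is large enough.

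**Step 4: the imbalance rule itself.** With six candidate covariates assumed (joint correlation 0.3 with the residual), a mechanical rule of adjusting for any covariate imbalanced at p < 0.05 gave type I error of 0.039 to 0.051 across the settings of Steps 2 and 3. Applied mechanically, the rule does not inflate false positives. Its defect is that the model is not fixed in advance and is not chosen for precision.

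**The case against.** The strongest reply is that the section is three short paragraphs of a journal article. It does not name practice, but it does not exclude it either. An analysis plan that is not shown may include practice and may fix the covariate list. This stands as far as practice is concerned: silence is not a decision, and practice alone would be a point to confirm. It does not dispose of the covariate rule, which the article states. An analysis plan with a prespecified list would have to depart from that sentence.

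Three stronger readings are tempting, and the protocol does not support them.

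- A reader might infer that the trial's confidence intervals will be mis-stated. That needs lists balanced within practice, which is not stated, and a non-zero residual ICC, which is not given. Practices are drawn from the same end of the deprivation ranking in one region, and baseline CASP-19 is already in the model, so part of any practice difference is absorbed. Where the error does occur it is conservative: intervals slightly too wide, with no excess of false positives.
- A reader might infer an inflated type I error from flexible adjustment. Choosing the most favourable of 64 covariate subsets after seeing results would raise it to about 0.09, or 0.14 if the covariates are more prognostic (joint correlation 0.5). The wording does not rule this out, but the protocol does not propose it.
- A reader might compute the chance that some covariate looks imbalanced, for example 1 − 0.95¹⁵ = 0.54 for 15 variables. The protocol states no significance tests of baseline variables, no 5% threshold and no set of 15, and the sum assumes independence. It also counts chance differences and does not measure error in the result.

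**Conclusion.** The point holds as a weakness in how the primary model is specified, not as a threat to validity. The firm part is the stated rule: covariates enter because of observed imbalance, so the model depends on the data and is not chosen for prognostic value. The part about practice is conditional. With lists balanced within practice, leaving it out makes the standard error 0.5% to 2.6% too wide at an ICC of 0.01 to 0.05, and 5.4% at 0.10. Power forgone is 0.8 percentage points at 0.05 and 1.6 at 0.10. With unblocked lists there is no bias. These sizes rest on 20 equal practices, a two-sided 5% level, the protocol's SD, correlation and attrition, and an assumed ICC. A change is worth making because a better model is available at almost no cost.

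**What to change.** State the primary model as 24-month CASP-19 on arm, baseline CASP-19 and general practice (fixed effect or random intercept), plus any prognostic covariates, all named before allocation is linked to outcomes. Use the same practice term for secondary outcomes where the model allows; sparse binary outcomes may not support it. Keep adjustment for covariates found imbalanced only as a labelled sensitivity analysis. It would also help to say whether each practice's list is balanced, since that decides which case above applies.

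The cost is a sentence or two in the analysis section and up to 19 of about 637 degrees of freedom. If the lists are unblocked and practices hardly differ, fixed practice terms would widen the standard error by about 1.5% at most (Step 3). A random intercept should limit that loss. The sample size stays at 750.
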